## Methods: Participants, interventions, and outcomes

### Study setting {9}

The study is conducted in the rural region around Vechta, a town in the northwestern part of Germany. The data collection is done at a cooperating specialized diabetes center in Vechta while trackers are worn by participants during everyday life.

### Eligibility criteria {10}

#### Inclusion criteria:

All participants have to provide written informed consent before enrollment in the study. Having a smartphone and internet access is required for study participation to ensure data collected with the tracker-based device can be transmitted to the research institution.

#### Exclusion criteria:

For safety reasons, the general exclusion criteria are age < 18 years, legal guardianship, pregnancy, and an increased risk of falling. In addition, diabetes patients with the following comorbidities and contraindications are excluded [13]: peripheral neuropathies, diabetic foot syndrome, myocardial infarction or stroke diagnosed in the previous 4 weeks, insufficiently controlled high blood pressure (≥140/90 mm Hg), hypoglycemia perception disorders, psychiatric disorders, poorly controlled T2DM (≤ 3 weeks therapy), severe sensorimotor and/or autonomic neuropathy, and unstable proliferative retinopathy.

### Who will take informed consent? {26a}

All individuals interested in participating in the trial receive an information sheet with detailed descriptions of the procedures, objectives, possible harms as well as benefits, and contact people related to the trial. Trained study personnel are available to answer questions regarding the trial and for explaining the procedures in detail. In addition, there are separate information sheets for healthy individuals and individuals with T2DM to provide precise information regarding possible risks associated with participation in the trial. The study personnel will obtain written informed consent from all individuals willing to participate in the trial.

### Additional consent provisions for collection and use of participant data and biological specimens {26b}

Detailed information about data collection procedures and the use and protection of participant data are provided on the information sheet. No additional consent is obtained because no ancillary studies or studies involving biological specimens are planned.

## Interventions

### Explanation for the choice of comparators {6b}

Because there are no suitable sham or placebo interventions, participants in the control group do not receive any intervention. In the intervention group, participants wearing only the tracker-based device are compared with participants wearing the tracker-based device and receiving a digital behavioral intervention via a smartphone app. This procedure is chosen to analyze the sole effect of the tracker and to determine a possible additional effect of a digital behavioral intervention accompanying the tracker-based intervention. All participants in the trial are given a brochure with detailed information about the relevance of physical activity for their health and national physical activity recommendations for different age groups [38] to strengthen their participation.

### Intervention description {11a}

The intervention group receives an activity tracker-based open-source smartwatch that is freely programmable [39–41]. Hence, firmware and applications specifically programmed for this study are used in order to comply with data protection and data security requirements. All device sensors that are not needed for the study are switched off for the entire study period.

The device will be tested in a separate study before the start of the main study to assess its accuracy and reliability. This assessment will involve a two-step process: (1) use under standardized laboratory conditions on a treadmill and (2) use under real-life conditions for 1–2 consecutive days. Participants (*n*=30) will wear the device and two reference devices (GT9X) on their wrist and hip. The Actigraph GT9X accelerometer is widely used in scientific studies to measure physical activity and shows good validity and reliability [42, 43]. The goal of this validation study is to define accurate cut-points and algorithms to detect physical activity levels (light, moderate, and vigorous) and steps. Further pre-studies with university students (*n*=25) wearing the tracker for 1 week will be conducted to assess the functioning as well as usability of the device and app, the practicability of the study design, and the questionnaires.

The smartwatch is linked to a smartphone app that is developed specifically for this study to protect the privacy of the participants and that transfers activity tracker data securely to the university server. In addition, the app is scientifically based and therefore provides the participants with assistance via behavior change techniques (BCT) that have been proven to be effective in changing behavior, specifically through self-monitoring, goal setting, and feedback [44–46]. Therefore, the app displays the steps and low, moderate, and vigorous physical activity in minutes per day (BCT “self-monitoring”), which are measured by the tracker-based device for each participant wearing the smartwatch. In addition, 50% of the participants wearing the tracker can set goals for themselves (BCT “goal-setting”) in terms of the physical activity levels they want to reach with the help of the app.

All participants in the intervention group receive a standardized introduction to the use of the device and the smartphone app as well as an instruction manual. In addition, qualified personnel will be trained to answer questions about the use of the device and the app and to offer support during weekly consultation hours until the end of the study in the case of technical problems.

### Criteria for discontinuing or modifying allocated interventions {11b}

Study participation does not affect medical treatment of diabetes patients, and the assignment of the patients to the intervention or control group does not have any effect on medical treatment in the diabetes center. Owing to regular visits to the center in line with the routine treatment, possible harms associated with the study can be monitored on a regular basis. Decisions about study drop-out due to medical reasons are based on the involved medical professionals’ judgment. The risks associated with monitoring and changing physical activity behavior are regarded as minor. The risk of hypoglycemia due to exercise is mentioned in the introduction to the device, and strategies are presented to reduce the risk. Patients who are at particularly high risk for hypoglycemia are excluded from participating in this study.

### Relevant concomitant care permitted or prohibited during the trial {11d}

Because it is not possible to prevent participants from taking part in classes or other interventions that promote a healthy lifestyle, the participation in such interventions is queried at each measurement point and the results of the statistical analyses will be adjusted for such effects if necessary.

### Provisions for post-trial care {30}

Because the conduct of this study does not affect the medical treatment of the study participants and the risks associated with trial participation are negligible, no ancillary or post-trial care, irrespective of the routine care of the diabetes patients, are provided.

### Outcomes {12}

The primary outcome is a change from baseline of moderate and vigorous physical activity in minutes or steps per week. Therefore, moderate and vigorous physical activity levels are aggregated and measured by one continuous variable. Physical activity is measured continuously with the tracker-based device, and algorithms are implemented to calculate amounts of different intensities [41]. Intensity levels are defined in accordance to intensity classification of Freedson et al. [48].

In addition, physical activity is assessed with questionnaires at four time points (*t*_0_, *t*_1_, *t*_2_, and *t*_3_).

As the analysis of the patient-relevant outcomes morbidity, mortality, and comorbidity of diabetes patients requires long-term studies, which are not feasible in this study due to limited project resources, the clinical outcomes HbA_1c_, body weight, and blood pressure are used as relevant surrogate parameters for these outcomes [13]. Therefore, secondary endpoints are medical parameters (HbA_1c_, TIR (time in range), BMI, and blood pressure). As covariates, psychosocial parameters (generic or diabetes-specific: health-related life satisfaction, self-efficacy, motives, volition, stages of behavioral change, personality, intention, and self-concordance), socio-demographic variables (age, gender, family background, family status, and socio-economic status), physical and mental health, comorbidities, alcohol as well as tobacco consumption, nutritional awareness, usage behavior and user satisfaction (with regard to the activity tracker and smartphone app), diabetes disease and treatment (e.g., medication), participation in external interventions, and severity of the disease are considered. The medical parameters of the healthy individuals are measured at four time points and those of the diabetes patients are collected via routine visits at the cooperating diabetes center. The data about covariates are captured with questionnaires at the same four time points. The items of the questionnaires originate from validated instruments.

In general, changes in the arithmetic means and variances of these mentioned outcomes from baseline are analyzed and compared between the intervention and control groups as well as between the four time points.

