### Sample size {14}

The sample size was calculated according to the primary hypothesis. The correlation between the results of the different measurement times is estimated to be 0.33 based on similar studies [66]. Regarding the effect size, the results of similar studies show that a medium effect can be assumed, which is why the effect size is estimated at *d*=0.5 and *f*^2^=0.15 [27, 28, 33, 66]. A dropout rate of 15% is derived from one of these studies [66]. For a power (1-β) of 0.8 with a significance level of *α*=0.05, assuming an effect size of *f*^2^=0.15, an adjustment with design effect, and a drop-out rate of 15%, a sample size of at least 1642 participants is necessary. With the help of the results of the pre-studies, a more precise calculation of the sample size is possible and the sample size can be adjusted if necessary.

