Since comparisons between participants in the intervention and control groups as well as comparisons of participants at different time points take place, a linear mixed model with two levels will be calculated to test the primary hypotheses [78]. The dependent variable is moderate and vigorous physical activity per week measured with a questionnaire. In the linear mixed model, time (*t*_0_ to *t*_3_) is the intra-class factor, and grouping (intervention group with tracker-based device, intervention group with tracker-based device and digital behavior intervention, and control group) is the inter-class factor [78]. The covariates psychosocial factors, socio-demographic factors, physical and mental health, comorbidities, alcohol and tobacco consumption, nutritional awareness, usage behavior and user satisfaction (with regard to the activity tracker and app), diabetes disease and treatment, participation in external interventions, and severity of the disease are assessed as categorical variables. Random intercepts are assumed while all other effects are regarded as fixed. The null model will be calculated and compared with alternative models regarding its fit via Akaike and Bayesian information criterion [78, 79]. Further, interactions will be considered and will be included in the model if the explanatory power of the model is strengthened. The same analysis will be performed for the assessment of secondary endpoints. Effects of all analyses will be considered significant if *p* < 0.05. All assumptions of the statistical tests will be checked in advance graphically and by appropriate tests. Bonferroni correction will be applied to counteract the problem of multiple testing [80].

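### If the arm effect is read as a difference in change from baseline, its variance at the planned correlation of 0.33 is about 50% larger than with baseline adjusted for

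*Protocol article*

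**What the plan says.** Three sections of the protocol article bear on this point.

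- **Outcomes {12}.** "The primary outcome is a change from baseline of moderate and vigorous physical activity in minutes or steps per week". The section closes by saying that, in general, "changes in the arithmetic means and variances of these mentioned outcomes from baseline are analyzed and compared between the intervention and control groups".
- **Sample size {14}.** "The correlation between the results of the different measurement times is estimated to be 0.33 based on similar studies".
- **Statistical methods {20a}.** "a linear mixed model with two levels will be calculated to test the primary hypotheses". "The dependent variable is moderate and vigorous physical activity per week measured with a questionnaire", so the outcome exists in all arms, including the controls who wear no device. In this model "time (*t*_0_ to *t*_3_) is the intra-class factor", which makes baseline one of the responses, and the three-level grouping is the between-subject factor. "Random intercepts are assumed while all other effects are regarded as fixed". The covariate list is long but does not contain baseline physical activity, and no equality of arms at t0 is stated. Interactions enter only if they make the model explain more. The secondary endpoints get the same analysis.

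**The concern.** When t0 is a response and the arms are free to differ there, the complete-data group-by-time contrast is exactly the difference in mean change from baseline. That contrast subtracts the whole baseline value, which amounts to a slope of 1. At a correlation of 0.33 and equal variances, the slope that best predicts follow-up from baseline is 0.33. The change score therefore adds more baseline noise than it removes, and it over-corrects any chance imbalance at t0. Randomisation makes the arms equal at t0 in expectation, and an unconstrained model does not use that information.

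Intervals for the between-arm effects would be wider than they need be. This matters most for the contrast of tracker alone against control, which has only half of the intervention group.

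A related point concerns the covariance. A random intercept alone imposes one correlation on visits 3, 6 and 9 months apart. If correlation falls with time, the standard error at 9 months is too small, and that is the visit that speaks to sustained improvement.

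**Working it through.** **Inputs from the protocol.** Correlation rho = 0.33, d = 0.5, f² = 0.15, dropout 15% and N = 1642 (Sample size {14}); 1:1 allocation with the intervention arm halved (Trial design {8}); SMD 0.17 for moderate-to-vigorous activity with a wearable alone (Background and rationale {6a}).

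**Assumptions.** Equal variance at all visits, complete data, two-sided 5% level without Bonferroni correction.

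**The plan's own figure.** The total of 1642 could not be reproduced. The design effect is not given; taking it as 1+3×0.33 = 1.99:
- d = 0.5 needs 126 to 128 in total, or about 295 to 300 after ×1.99 and ÷0.85.
- f² = 0.15 with 1 to 40 tested predictors needs 55 to 214, or about 129 to 501 after both.

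Values near 1642 appear only with choices that the article does not state. The variance comparison below does not use this figure.

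**Variance of the arm contrast at one follow-up visit,** in units of sigma²(1/n1+1/n2):
- Change from baseline: 2(1-rho) = 2×0.67 = 1.340
- Follow-up only: 1.000
- Baseline adjusted or constrained: 1-rho² = 1-0.1089 = 0.891

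The ratio 1.340/0.891 is 1.50. The reduction is 1-(1+rho)/2 = (1-rho)/2 = 33.5%. The standard error is multiplied by √0.665 = 0.815, which is 18.5% less. Generalised least squares on four visits with common correlation 0.33 gives the same values. A simulation of 4,000 trials gave a 33.9% reduction.

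**Dependence on rho,** from (1-rho)/2:

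| rho | reduction |
|---|---|
| 0.2 | 40% |
| 0.33 | 33.5% |
| 0.5 | 25% |
| 0.7 | 15% |
| 0.9 | 5% |

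**If only a group main effect is fitted.** The mean of four visits has variance (1+3×0.33)/4 = 0.4975. Including t0 dilutes a constant post-baseline effect to three quarters, so the variance per unit effect is 0.4975/0.75² = 0.884. The constrained mean of t1 to t3 has (1+2×0.33)/3-0.33² = 0.444. The loss is then larger, at about half.

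**Power.** The number analysed is 1642×0.85 ≈ 1396, or 698 control, 698 intervention, and 349 on tracker alone.
- Pooled intervention against control: SE √(1.34×2/698) = 0.062 against √(0.891×2/698) = 0.051. At SMD 0.17, power is 78% against 92%.
- Tracker alone against control: SE √(1.34×(1/349+1/698)) = 0.076 against 0.062. At SMD 0.17, power is 61% against 78%.
- At d = 0.5, even the largest of these SEs gives 0.5/0.076 ≈ 6.6, so power exceeds 99.9% either way.

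**Covariance (illustration).** Assume correlations of 0.45, 0.33 and 0.20 at lags of 3, 6 and 9 months. The random-intercept model pools them to (3×0.45+2×0.33+0.20)/6 = 0.368. For t3 against t0 the true factor is 2(1-0.20) = 1.60 and the model's is 2(1-0.368) = 1.264. The ratio of standard errors is √(1.60/1.264) = 1.125, the effective critical value is 1.96/1.125 = 1.74, and the type I error is about 8.2%. The same steps give 3.6% at t1 and 5.7% at t2. With no decay, all three are 5%.

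**The case against.** The strongest reply is that the contrast is inferred. The statistical methods do not fix a group-by-time term, the sentence in Outcomes {12} is a general one that covers all outcomes, and the hypothesis in Objectives {7} is an increase over time in the tracker groups, a within-group change to which this comparison does not apply. This stands as a limit: 1.50 belongs to one reading of the model. It does not remove the point, because Outcomes {12} and the model both provide for arm comparisons, and the main-effect reading loses more. Only a follow-up-only contrast, which the document does not describe, would gain less (10.9%).

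How baseline enters a model is also often left to an analysis plan. Here, though, the article itself states the responses, the covariates and the random-effect structure.

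Several stronger readings are not supported:

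- **That the planned analysis is biased or invalid.** A difference in change scores is unbiased under randomisation and, with a correct covariance, keeps its type I error.
- **That 1.50 converts into participants saved.** The total of 1642 does not follow from the stated inputs, so a head-count has no firm base.
- **That the trial as planned lacks power for this reason.** At d = 0.5 it does not. The SMD of 0.17 is cited as not statistically significant and refers to a wearable alone, so applying it to the pooled arm is only indicative.
- **That the gain is unconditional.** Participants are randomised at baseline and not blinded, and the article does not say that the t0 questionnaire precedes allocation.
- **That secondary endpoints gain as much.** No correlation is given for them, and a stable measure such as BMI may gain little.
- **That type I error at 9 months is inflated.** The protocol gives one correlation, and the 8.2% rests on one assumed set. The plan also provides for model comparison by information criteria and for checks of assumptions.

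**Conclusion.** The point holds as an efficiency improvement that should be made. Read as a group-by-time contrast, the between-arm analysis has a variance about 50% larger than it needs, and at the protocol's own correlation it is less precise than ignoring baseline. The available reduction is 33.5% in variance and 18.5% in standard error. This rests on rho = 0.33, equal variances over time, and t0 values unaffected by allocation. It concerns the questionnaire outcome only, since controls have no tracker data. The practical value lies in effects well below d = 0.5.

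The covariance point is secondary and conditional. Any fall in correlation with time between visits makes the 9-month standard error too small, but the protocol gives no basis for saying by how much.

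**What to change.** In Statistical methods {20a}, specify the between-arm analysis in one of two ways:

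1. Questionnaire activity at t1 to t3 as the response, with t0 activity as a covariate and group-by-time terms.
2. All four visits as responses, with a common t0 mean across arms and group effects only at t1 to t3.

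State the contrast in advance rather than admitting it on model fit. Confirm and state that the t0 questionnaire is completed before allocation is known; a common t0 mean is safe only on that condition. Treat HbA1c, BMI and blood pressure in the same way, each with its own baseline.

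Replace the random intercept alone with an unstructured covariance over the visits modelled. For four visits that is 10 parameters instead of 2, which is negligible with about 1,400 participants.

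Report the expected gain as a variance ratio with its dependence on rho, and say that it matters for effects well below the planned d = 0.5. The cost is a change of model formula; no extra data or participants are needed.

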### Participant timeline {13}

Participants who give their informed consent and fulfill the inclusion criteria are assessed at four timepoints (see Table 1 and Fig. 1). At baseline, a questionnaire with socio-demographic questions [51] is administered, and at all four time points, a questionnaire with health-related questions [52], questions regarding physical activity [53, 54], a psychosocial questionnaire [55–64], and questions regarding the use of tracker-based devices and apps outside this study is administered. In addition, the diabetes parameters are measured in a standardized way by qualified study personnel at all four time points. Questions regarding the usability of and satisfaction with the app and the tracker-based device [65] are asked after 6 months and regarding the follow-up use of the device after 9 months.

**Table 1 Tab1:**
[figure not shown]
Participant timeline

**Fig. 1 Fig1:**
[figure not shown]
Graphical representation of the study design according to Consolidated Standards of Reporting Trials (CONSORT, [49, 50])

At baseline, participants are randomly assigned to either the intervention or the control group. For participants in the intervention group wearing the tracker-based device, physical activity is measured continuously with the device for 6 months. For the remaining 3 months, participants can decide on their own if they want to continue wearing the tracker until t_3_. At t_3_ they have to return the tracker to the study personnel.

### Sample size {14}

The sample size was calculated according to the primary hypothesis. The correlation between the results of the different measurement times is estimated to be 0.33 based on similar studies [66]. Regarding the effect size, the results of similar studies show that a medium effect can be assumed, which is why the effect size is estimated at *d*=0.5 and *f*^2^=0.15 [27, 28, 33, 66]. A dropout rate of 15% is derived from one of these studies [66]. For a power (1-β) of 0.8 with a significance level of *α*=0.05, assuming an effect size of *f*^2^=0.15, an adjustment with design effect, and a drop-out rate of 15%, a sample size of at least 1642 participants is necessary. With the help of the results of the pre-studies, a more precise calculation of the sample size is possible and the sample size can be adjusted if necessary.

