### Trial design {8}

The monocentric, pragmatic RCT has a parallel group design with an allocation ratio of 1:1. Tests of equivalence will be performed to compare the intervention group wearing a smartwatch with an activity tracker in everyday life with the control group that does not wear the device. Furthermore, 50% of the participants in the intervention group will also receive a digital motivational intervention via a smartphone app. The planning and implementation of the study is orientated towards the Declaration of Helsinki [37].

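### The stated sample-size inputs do not give 1642: with the only design effect the article supports they give about 130 to 300 participants

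*Protocol article*

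**What the plan says.** The Sample size section says the number was derived for the primary hypothesis. Its inputs are:

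- Error rates: "For a power (1-β) of 0.8 with a significance level of *α*=0.05".
- Effect: called medium, "which is why the effect size is estimated at *d*=0.5 and *f*^2^=0.15". Only f² = 0.15 is carried into the sentence that gives the result.
- Correlation: "The correlation between the results of the different measurement times is estimated to be 0.33".
- Inflation: a design effect whose size is not given, and 15% dropout.

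The result is stated as "an adjustment with design effect, and a drop-out rate of 15%, a sample size of at least 1642 participants is necessary". The section adds that the number may be refined after the pre-studies. The abstract and the Discussion repeat 1642.

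Two other places describe the structure that a design effect would have to reflect. Trial design: "The monocentric, pragmatic RCT has a parallel group design with an allocation ratio of 1:1". Statistical methods: "a linear mixed model with two levels will be calculated to test the primary hypotheses", with time from t0 to t3 as the within-person factor, three groups and random intercepts.

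**The concern.** The passage states a result and names what it was computed from, so the result can be checked. A medium effect at 80% power normally needs of the order of a hundred evaluable participants. Going from there to 1642 after 15% dropout requires a very large multiplier, and the design effect is the only input left to supply it.

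The trial has one centre, randomises individuals within disease strata and models visits within persons, so no cluster of the necessary size is visible. If the multiplier has no source, the effect size, the 80% power and the claim that 1642 are necessary cannot all hold. Readers and the ethics committee would then have a wrong account of why this many people are enrolled. They would also not know that statistical significance can be reached at effects well below the one used for planning.

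**Working it through.** **Inputs.** α = 0.05, taken as two-sided because the article does not say. Power 0.80, f² = 0.15, d = 0.5, correlation 0.33 and dropout 15% come from Sample size. Four visits and three groups come from Statistical methods. The 1:1 ratio and the half split of the tracker group come from Trial design. The number of tested terms (u) is not stated, so a range is shown.

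**1. The two effect sizes.** For two equal groups f² = d²/4.
- d = 0.5 gives f² = 0.25/4 = 0.0625.
- f² = 0.15 gives d = 2 × √0.15 = 0.77.
- On the same contrast they differ by 0.15/0.0625 = 2.4 in f².

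**2. Participants needed before inflation.** For f² = 0.15: noncentral F test with noncentrality f² × N. For d = 0.5: two-sample t test, 64 per group.

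**3. The plan's own figure.** Evaluable after dropout: 1642 × 0.85 = 1395.7, about 1396. The design effect needed to reach 1642 is 1396/N. The only one the stated inputs support, in its most inflating standard form, is 1 + (4 − 1) × 0.33 = 1.99.

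| Case | N evaluable | Design effect needed for 1642 | Total with 1.99 and 15% dropout |
|---|---|---|---|
| f² = 0.15, u = 1 | 55 | 25.4 | 130 |
| f² = 0.15, u = 2 (three groups) | 68 | 20.5 | 160 |
| f² = 0.15, u = 3 | 77 | 18.1 | 182 |
| f² = 0.15, u = 11 (three groups by four times) | 123 | 11.3 | 289 |
| d = 0.5 | 128 | 10.9 | 300 |

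The last column is N × 1.99, rounded up, divided by 0.85 and rounded up. Example: 55 × 1.99 = 109.5, so 110; 110/0.85 = 129.4, so 130.

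With Bonferroni for six tests (α = 0.05/6) the totals are 200 to 399 for f² = 0.15 with u = 1 to 11. For d = 0.5, by the normal approximation, N = 194 gives 456.

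So 1642 is 1642/300 = 5.5 to 1642/130 = 12.6 times the derived number, and 1642/456 = 3.6 times in the most demanding of these variants.

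**4. What 1642 does match.** Treat 0.15 as a standardised mean difference with no design effect:
- per arm 2 × (1.960 + 0.842)²/0.15² = 697.7
- 697.7/0.85 = 820.8, rounded up to 821
- 821 × 2 = 1642, exactly.

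**5. What 1642 delivers.** With 1396 evaluable: 698 control and 698 tracker, the latter split 349 and 349. Detectable difference at 80% power is k × √(1/n₁ + 1/n₂), where k = 2.80 at unadjusted 5%, 3.24 for three Bonferroni tests and 3.48 for six. No design effect:

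| Contrast | Unadjusted | 3 tests | 6 tests |
|---|---|---|---|
| Pooled tracker v control (698 v 698) | 0.15 SD | 0.17 | 0.19 |
| Tracker alone v control (349 v 698) | 0.18 SD | 0.21 | 0.23 |
| Between tracker arms (349 v 349) | 0.21 SD | 0.24 | 0.26 |

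With a design effect of 1.99 the effective total is 1396/1.99 = 702, and the pooled value at unadjusted 5% is 2.80 × 2/√702 = 0.21 SD. Power at d = 0.5 for the pooled comparison at unadjusted 5% is above 99.9% with a design effect of either 1 or 1.99.

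**The case against.** The best defence is that this is a condensed article. It says a design effect was applied without printing its value or the number of predictors, so the full working may be sound. Routes to 1642 through unstated inputs can be built:

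- 128 × 10.9/0.85 = 1641.4, where 10.9 = 1 + 30 × 0.33. This needs clusters of 31 at the stated correlation, and it uses d = 0.5, not the f² = 0.15 named in the calculation.
- Powering each of the three disease groups separately at f² = 0.15, with design effect 1.99 and 15% dropout, gives 1503, 1587 and 1672 for 40, 45 and 50 tested predictors. Statistical methods does list about a dozen covariate families, treated as categorical.

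These routes cannot be excluded, but the article states neither. The correlation of 0.33 is between measurement times, not between members of a cluster. Disease status enters the model as a dummy variable, with no mention of powering each stratum. Leaving detail to a full protocol is acceptable. Here, though, the article asserts a result from named inputs, and those inputs lead elsewhere.

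Two parts of the defence stand. First, d = 0.5 and f² = 0.15 are the conventional medium labels of two test families. They conflict only if both describe the same two-group contrast, so a reader who infers an outright contradiction goes too far. Second, a single set of replacement figures would be unsafe: the detectable effects depend on the Bonferroni correction that the plan announces and on whether a design effect applies. If one of 10.9 really did apply, power at d = 0.5 would be about 81%, not above 99.9%.

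**Conclusion.** The concern holds in this form: the claim that f² = 0.15, 80% power, α = 0.05, a design effect and 15% dropout make 1642 necessary does not follow from what the article states. The stated inputs give about 130 to 300 participants, or up to about 460 with Bonferroni for six tests. This rests on two-sided α, 1 to 11 tested terms and a design effect of 1.99. Only an unexplained design effect of about 11 to 25 closes the gap.

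Three stronger readings are tempting and not supported:

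- **That the trial is underpowered.** The discrepancy runs towards too many participants for the stated effect.
- **That the plan enrols ten times too many.** The ratio is about 5 to 13, or 3.6 with Bonferroni for six tests. It concerns what the stated inputs require, not whether a trial of this size is worthwhile for smaller effects.
- **That 0.15 was entered on the wrong scale.** The exact match with a standardised difference of 0.15 suggests this, but the article does not say so and coincidence cannot be ruled out.

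**What to change.** Keep 1642 and correct the justification in Sample size:

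1. Use one effect metric, tied to the contrast that is tested. If d = 0.5 on the two-group contrast is meant, the matching value is f² = 0.0625.
2. Give the design effect's value and the cluster it represents, and add that cluster to the mixed model. If it has no source, remove it. It should not be deleted before the team has checked what it was.
3. State the sidedness, the number of tested terms and the number of tests in the Bonferroni correction.
4. Replace the 80% sentence by what 1642 randomised (1396 evaluable) delivers under the planned analysis. If no design effect applies, an example at unadjusted two-sided 5% is: 80% power for about 0.15 SD for pooled tracker versus control, 0.18 SD for tracker alone versus control and 0.21 SD between tracker arms. Use the Bonferroni values above for three or six tests, and about 0.21 SD pooled at unadjusted 5% if a design effect of 1.99 applies.

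The cost is one reworded passage. Enrolment does not change.
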